# Comparative effectiveness of in-person vs. remote delivery of the Common Elements Treatment Approach for addressing mental and behavioral health problems among adolescents and young adults in Zambia: protocol of a three-arm randomized controlled trial

**DOI:** 10.1186/s13063-022-06319-4

**Published:** 2022-05-19

**Keywords:** Global mental health, Adolescents, Randomized controlled trial, Telehealth, Zambia, Implementation science

## Abstract

**Background:**

In low- and middle-income countries (LMIC), there is a substantial gap in the treatment of mental and behavioral health problems, which is particularly detrimental to adolescents and young adults (AYA). The Common Elements Treatment Approach (CETA) is an evidence-based, flexible, transdiagnostic intervention delivered by lay counselors to address comorbid mental and behavioral health conditions, though its effectiveness has not yet been tested among AYA. This paper describes the protocol for a randomized controlled trial that will test the effectiveness of traditional in-person delivered CETA and a telehealth-adapted version of CETA (T-CETA) in reducing mental and behavioral health problems among AYA in Zambia. Non-inferiority of T-CETA will also be assessed.

**Methods:**

This study is a hybrid type 1 three-arm randomized trial to be conducted in Lusaka, Zambia. Following an apprenticeship model, experienced non-professional counselors in Zambia will be trained as CETA trainers using a remote, technology-delivered training method. The new CETA trainers will subsequently facilitate technology-delivered trainings for a new cohort of counselors recruited from community-based partner organizations throughout Lusaka. AYA with mental and behavioral health problems seeking services at these same organizations will then be identified and randomized to (1) in-person CETA delivery, (2) telehealth-delivered CETA (T-CETA), or (3) treatment as usual (TAU). In the superiority design, CETA and T-CETA will be compared to TAU, and using a non-inferiority design, T-CETA will be compared to CETA, which is already evidence-based in other populations. At baseline, post-treatment (approximately 3–4 months post-baseline), and 6 months post-treatment (approximately 9 months post-baseline), we will assess the primary outcomes such as client trauma symptoms, internalizing symptoms, and externalizing behaviors and secondary outcomes such as client substance use, aggression, violence, and health utility. CETA trainer and counselor competency and cost-effectiveness will also be measured as secondary outcomes. Mixed methods interviews will be conducted with trainers, counselors, and AYA participants to explore the feasibility, acceptability, and sustainability of technology-delivered training and T-CETA provision in the Zambian context.

**Discussion:**

Adolescents and young adults in LMIC are a priority population for the treatment of mental and behavioral health problems. Technology-delivered approaches to training and intervention delivery can expand the reach of evidence-based interventions. If found effective, CETA and T-CETA would help address a major barrier to the scale-up and sustainability of mental and behavioral treatments among AYA in LMIC.

**Trial registration:**

ClinicalTrials.govNCT03458039. Prospectively registered on May 10, 2021

## Background

The quality and availability of mental and behavioral health care in low- and middle-income countries (LMIC) are significantly deficient [1–3]. The high need and inadequate resourcing for mental health results in a substantial treatment gap [1, 2, 4] that directly contributes to the ongoing violation of human rights, abuse and neglect, reduced adherence to medical regimens, long-term disability, ill-health, lower economic productivity, and increased mortality [5–9].

Adolescents and young adults (AYA) in LMIC are in critical need of access to mental and behavioral healthcare. Mental and behavioral health problems account for up to 30% of disability-adjusted life years before the age of 30 [10]. AYA are disproportionately affected by the HIV epidemic, accounting for 30% of all new HIV infections [11]. In Zambia, the location of the current study, AYA are at high risk of HIV infection, poverty, experienced violence (including sexual and gender-based violence), and unemployment [12, 13]. The combination of past and continuing stressors can cause stress-related problems including maladaptive behaviors, emotional and/or behavioral dysregulation, cognitive challenges, substance use/abuse, aggression, risky sexual behavior, and difficulties with functioning [1, 14–20], which in turn increase the risk for a range of poor outcomes, including HIV/AIDS risk, substance abuse, and lower economic productivity [8, 21–23].

The body of research and policy supporting the effectiveness of mental health treatments is growing rapidly [24–28]. Research shows that certain mental health treatments are effective, acceptable, feasible, and can be implemented in LMIC with positive clinical outcomes using an apprenticeship model and a task-sharing approach where lay providers with limited formal mental health training function as counselors [24, 25, 28–31]. Despite this evidence, the wide-scale update and sustainability of non-professional delivered interventions in LMIC are virtually non-existent.

The Common Elements Treatment Approach (CETA) is an intervention that is flexible, transdiagnostic, and delivered by lay counselors or non-professionals in LMIC to address comorbid mental and behavioral health problems [29]. CETA is grounded in cognitive behavioral therapy elements common to evidence-based treatments (EBTs) for trauma, behavioral problems, anxiety, and depression [32]. This approach allows a counselor to decide on which element(s), order, and dose are most appropriate for each client based on presentation. Randomized controlled trials (RCT) have demonstrated the effectiveness of CETA for a range of mental health, substance use, and behavioral issues among adults in a variety of low-resource settings [33–38]. In a non-randomized study in Ethiopia, CETA improved mental and behavioral health problems improved among youth [39]; however, CETA has not yet been evaluated among adolescents in a fully powered randomized trial.

Trainings for EBTs, such as CETA, are typically provided by an “expert” who usually is a Ph.D. level expatriate with extensive experience and EBT purveyor-approved. After the trainings, the “expert” continues EBT supervision and coaching to ensure skill transfer and fidelity [40]. Multiple studies completed on EBTs in LMIC have demonstrated the use of expert-delivered training with the apprenticeship model is feasible and effective [24, 25, 28, 31]. However, scale-up and sustainability efforts of EBTs are nearly impossible when utilizing an expert-delivered training approach since experts are scarce, costly, have limited time, usually require a translator, and often need to travel long distances for on-site trainings, something that was particularly problematic during the COVID-19 pandemic.

A train the trainer (TTT) strategy is a specific form of capacity building designed to provide trainees with the necessary knowledge and skills to become trainers themselves—and, arguably, sustain a workforce over time. The TTT model has been effectively used in a diverse range of disciplines (e.g., education, health care) [41–44] and has involved multiple types of trainees (e.g., direct care counselors, parents, or teachers) depending on the complexity of skills being taught [45, 46]. However, there is limited research and few rigorous studies on whether TTT efforts achieve their desired level of change, particularly with mental health EBT [47]. Research also suggests that technology-based training approaches (i.e., video and audio-based instruction) may have the potential to result in comparable learning to face-to-face instruction across LMIC settings [48, 49]. Thus, applying technology-based training approaches to TTT may increase the scalability of EBTs [50, 51].

In addition to technology-based training of trainers, technology-based delivery of health interventions has been identified as a potential strategy to expand mental healthcare access in LMIC settings [52]. However, most of the evidence showing the efficacy of technology-based mental health delivery has been conducted in high-income countries (HIC) with only discussion of its implications for implementation in LMIC [53, 54]. The majority of studies in this area have focused on videoconferencing, with documented high satisfaction and acceptability of tele-mental health delivery for children and AYA that are underserved or located in rural areas [55–58]. During the COVID-19 pandemic, some mental health practitioners in upper-income countries transitioned almost universally to teletherapy. In various LMIC settings, tele-mental health delivery has been shown to be feasible [59, 60] and similar to HIC contexts and satisfactory comparable to in-person visits [61]. However, there is limited evidence on treatment effectiveness and symptom reduction with technology-based delivery relative to in-person implementation in limited-resource settings [61].

Tele-mental health delivery methods reduce common barriers to treatment access and adherence, including time, financial, and transportation demands, among hard-to-reach populations, particularly during public health crises. Given the rapid increase to access to mobile technology in recent years, tele-mental health delivery has become a viable option. In January 2021, there were over 19 million mobile phone subscriptions in Zambia, an equivalent of about 104% of the population [62]. In addition, previous technology-based healthcare delivery systems have found high user acceptance and increased adoption rates of mobile technology that is low-cost, readily available, culturally sensitive, and easy to operate [63]. Exploring technology options and models for treatment *delivery* is critical for providing and scaling up care in hard-to-reach populations and reducing the treatment gap in LMIC settings [64, 65]. Together, tech-delivered training and telehealth delivery can reduce the need for in-person logistic demands across the training and treatment cascade at the trainer, counselor, and client levels, increasing the feasibility, sustainability, and cost-effectiveness of evidence-based mental health care provision in LMIC settings.

Given the substantial mental and behavioral health treatment gap for AYA in LMIC and the potential for technology to improve the delivery and sustainability of EBTs, research into the effectiveness and feasibility of technology-based approaches to training and intervention delivery is warranted. In this paper, we describe the protocol for a randomized controlled trial to test the comparative effectiveness of traditional in-person CETA and telehealth-delivered CETA (T-CETA) featuring lay counselors trained by trainers through a technology-based TTT approach in reducing mental and behavioral health problems among AYA in an urban setting of Zambia.

## Methods

### Study setting

All study procedures will take place in Lusaka, Zambia. Participants will be recruited from community-based organizations that provide health, education, and social services to AYA in Lusaka. Organizations with access to AYA populations and with existing counseling/mental health services were selected, as they will serve as prime CETA and T-CETA service delivery points, should the study demonstrate feasibility and effectiveness in this population. Selected organizations include a combination of local and international non-governmental organizations (NGOs) and government health clinics. Heterogeneity in implementing sites is desirable to generate robust clinical and implementation evidence.

### Overview of study design

This study will use a hybrid type 1 three-arm parallel-group randomized controlled design [66] to compare the effectiveness of CETA delivered either in-person or via telephone (T-CETA), compared with a treatment as usual (TAU) control group. CETA trainers (up to *N* = 6) will be identified from an existing cadre of Zambian counselors and will be trained to be CETA trainers via a technology platform. They will be trained to facilitate technology-delivered CETA trainings to new prospective counselors (up to *N* = 50) recruited from our partnering organizations, who will be trained to deliver both in-person CETA and T-CETA. We will recruit and randomize AYA clients (*N* = 400) with mental and behavioral health problems from our partnering organizations to one of the following three conditions: (a) CETA, (b) T-CETA, or (c) TAU. We will evaluate mental and behavioral health outcomes among AYA at baseline, post-treatment (approximately 3–4 months post-baseline), and 6 months post-treatment (approximately 9 months post-baseline) (Fig. 1). Data will also be collected on CETA trainer and counselor competency, fidelity, and knowledge, and implementation constructs (e.g., acceptability, feasibility, cost) associated with training and intervention delivery.

**Fig. 1 Fig1:**
[figure not shown]
Spirit flow diagram of the trial schedule

### Participants

AYA participants will be between the ages of 15–29 with mental and behavioral health problems as measured by validated screening tools (see the “Screening and baseline assessment” section). Trainer and counselor participants will be lay providers interested in mental health training. Full eligibility criteria are summarized in Table 1.

**Table 1 Tab1:** Participant eligibility and screening

**AYA**	
1. 15–29 years of age	
2. Attend or be referred to the study site	
3. Live in the area served by a study site (i.e., not staying temporarily)	
4. Ability to speak one of the study languages (English, Bemba, or Nyanja)	
5. Screening: present with one or more common mental/behavioral health problems based on validated screening tools included in the audio computer-assisted self-interviewing (ACASI) system. Specifically, the following screening tools and cutoff values:	
a. Youth Self Report Internalizing Scale (≥ 14)	
b. Youth Self Report Externalizing Scale (≥ 8)	
c. Child PTSD Symptom Scale (≥ 12)	
6. Exclusion:	
a. Currently on unstable psychiatric drug regimen (e.g., altered in past 2 months)	
b. Suicide attempt or active and severe self-harm in the past month	
c. Psychotic disorder or severe mental illness	
**Trainers and counselors**	
1. 18 years of age or older	
2. Interest in providing CETA	
3. Time/availability to participate in the study	
4. Minimal education level is comparable to a high school education	
5. Ability to speak English fluently and speak at least 1 local language (Nyanja or Bemba)	
6. Completion of an in-person interview with study team investigators demonstrating strong communication skills	
7. Planning to stay in the study area (Lusaka) to provide treatment to clients and/or training to new counselors	
Trainers: in addition to all of the above:	
8. Interest in teaching CETA	
9. Completion of the CETA training	
10. Completion of a minimum of 3 CETA cases under supervision	

### Recruitment

For the recruitment of AYA clients, the research team will conduct half-day training sessions explaining CETA, and for whom and what problems it is appropriate, to all staff at collaborating partner organizations. In addition, a separate 2-h CETA information meeting will be conducted for home-based care workers that help link individuals to services. Recruitment by home-based care workers connected to partner sites is a process used previously by the research group to help identify, connect, and assure that those in need get services and mirrors how the program could recruit clients in a real-world setting [67, 68]. Initial contact will be made by the partner organization staff or home-based care workers who will explain the study with a recruitment script to AYA, and their primary caregiver for those under age 18, with whom they have previously or currently worked. Snowball recruitment methods may also be used to identify additional AYA participants. Recruitment will be conducted in private locations such as a private room in a community location (e.g., church, school) or a private room within the partner organization’s facilities. AYA that express interest in receiving more information on the study will be connected to the research team.

Trainer- and counselor-level participants will be recruited from our collaborating partners and through contacts of local stakeholders like the Ministry of Health to increase the likelihood that the provision of CETA continues after the end of the study period. Our collaborating partners and contacts will recommend the current staff who they think would be appropriate CETA counselors and have time to provide this service. Potential counselors will also need to submit a resume to the study team, a letter expressing their motivation to be a counselor, and a letter of support from their organization. The study staff will interview the applicants and ensure they meet the inclusion criteria. The final agreement will be by consensus of the study team and collaborating partners.

### Informed consent

Consent activities with all participants involve discussing relevant study details including the purpose, treatment details, privacy, and risks and benefits. Informed consent will be obtained from AYA clients (and caregivers, if applicable) in English, Bemba, or Nyanja by trained research assistants. Consent is obtained for participation in all study activities at the screening phase. AYA will be informed that study participation is voluntary and will not impact any ongoing or future services they may receive. Research assistants will be trained in human subjects and responsible for the conduct of research and receive appropriate certification. For clients under age 18, research assistants will also obtain informed consent and permission from the AYA’s primary caregiver to obtain assent from the AYA participant. Informed consent forms are available from the corresponding author on request.

### Screening and baseline assessment

The screening portion of the baseline assessment consists of demographic information, internalizing and externalizing symptoms, and post-traumatic stress. Screening instruments will be administered using the audio computer-assisted self-interviewing (ACASI) system. Participants can navigate through the questionnaires themselves using a laptop computer while listening to the questions through headphones and seeing the question and response options on the screen. A research assistant will be positioned nearby in case the participant has any difficulty. We have used ACASI extensively with AYA populations in Zambia and found it to be an acceptable and feasible approach for measuring mental and behavioral health outcomes [69]. All measures included in the ACASI have previously been used by our team with similar study populations and are available in English, Bemba, and Nyanja [35, 68–72].

#### Broadband Mental Health Functioning (Youth Self Report (YSR) [72];)

The YSR is a 112-item measure of broadband mental health symptoms on a 3-point Likert scale (*0 = not true, 1 = somewhat true, 2 = very true or often true*). The measure produces 8 subscales and two broad internalizing and externalizing symptom scores. Eligibility cutoffs of ≥ 14 and ≥ 8 will be used for the internalizing and externalizing subscale scores, respectively, based on our previous validity study [73].

#### Post-traumatic stress symptoms (Child PTSD Symptom Scale (CPSS) [74];)

The CPSS is a 17-item scale that corresponds to the DSM-5 criteria for PTSD on a 4-point Likert scale (*0 = not at all or only one time, 1 = once a week or less/once in a while, 2 = 2 to 4 times a week/half the time, 3 = 5 or more times a week/almost always*). The items produce a total Symptom Severity Scale. Based on our previous validity study in Zambia, an eligibility cutoff of ≥12 will be used [73].

Participants who do not meet the eligibility cutoffs on screening measures will exit the study and be provided resources for mental health and other social services in their area. Eligible AYA participants will continue to complete the second portion of the baseline assessment via the ACASI system, which includes measures of substance use, aggression/violence, functioning, and COVID-19 vaccine hesitancy (see the “Outcomes” section).

### Randomization and blinding

Each participant will be assigned a unique ID number by the research assistant during the screening/baseline assessment. Randomization will occur at the individual AYA level and be stratified by site. Following the determination of eligibility and completion of the baseline assessment, the research assistant will communicate the ID number to a study staff based at research headquarters who will not interact with study participants. This study staff will maintain a randomization sequence that will be developed a priori by a US-based research staff. This list will not be available or viewable to data collectors in Zambia. The list will have a sequence of treatment assignments (CETA or T-CETA or TAU) in random order, stratified by site, produced via a random number generator in Microsoft Excel. Randomization will be imbalanced (1.5 CETA: 1.5 T-CETA: 1 TAU) due to the different sample size requirements in the TAU control arm (see the “Data analysis” section). Eligible AYA participants will be assigned a condition based on the next available slot on the randomization list and inform the field staff of the assignment. At this point, the field staff will not be blinded to condition assignment for participants they assess. Eligible AYA clients will be informed immediately of the result of the randomization and appropriate next steps: CETA and T-CETA participants will be told that a counselor will be contacting them within 48 h to set up the first session; TAU participants will be told that the study team will contact them in approximately 3 months to schedule their first post-assessment. The use of ACASI will result in the outcome assessments being blinded; data analysts will also be blind to the intervention status when conducting analyses. Due to the nature of the intervention, neither counselors nor AYA clients will be blinded.

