### Outcomes

The primary outcomes in the trial will be AYA trauma symptoms (as measured by the CPSS), internalizing symptoms, and externalizing behaviors (both measured by the YSR) administered via ACASI as described in the “Screening and baseline assessment” section. Secondary outcomes among AYA, also administered via ACASI, include substance use, which will be measured with the Alcohol, Smoking, and Substance Involvement Screening Test (ASSIST) [67, 77] and aggression/violence as measured by the Youth Victimization Scale [78]. Outcomes are assessed at baseline, post-treatment completion (approximately 3–4 months post-baseline for TAU participants), and 6 months post-treatment completion (approximately 9 months post-baseline for TAU participants). The primary time point is post-treatment.

In addition to AYA outcomes, we will collect preliminary data on counselor and trainer competency, fidelity, and knowledge. This will be collected at various points throughout the study through standardized role-plays and CETA knowledge tests. Mixed methods interviews will be conducted among clients, counselors, and trainers to explore the acceptability and feasibility of CETA training and delivery. We will also collect data on health utility among AYA using the EuroQol 5-Dimensions for Youth (EQ-5D-Y) [79, 80] to inform the cost-effectiveness analyses. In all, AYA participants will be engaged in the study for approximately 9–12 months.

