## Discussion

Scalable systems of care, such as those being tested in this trial, are needed to close the mental health treatment gap in LMIC, particularly for populations at-risk for poor outcomes and low treatment adherence, such as adolescents and young adults. The need for telephone-based mental health services in LMIC has become widely discussed during the COVID-19 pandemic. Significant barriers to scale-up of evidence-based treatments in LMIC include a lack of feasible, sustainable training for local lay providers, and client access to care. This will be the first CETA trial that is specifically designed to evaluate the treatment effectiveness among an adolescent population and the first to feature a technology-based training modality and a telehealth delivery. This study is a first step to build a system of technology-driven training and treatment provision to expand access to evidence-based mental healthcare in Zambia and other LMIC settings. The need for effective, remotely delivered interventions is particularly relevant in the COVID-19 era.

There are several notable limitations to this study. First, this trial has a risk of social desirability bias in AYA reporting of symptoms, particularly in the CETA treatment arms given their therapeutic relationship with counselors. To combat this risk, we are using a standardized ACASI assessment system to measure symptoms at all time points, administered by research assistants and not by the counselors themselves. Second, this trial is occurring across several urban sites in the capital city of Zambia, and our participants will not be representative of AYA in more rural areas of Zambia and across other rural LMIC settings. Additional research will be needed on the delivery of these interventions to rural populations where T-CETA may actually be more feasible and acceptable because of access to private space and the high costs of transportation to a clinic.

If the CETA technology training platform is deemed feasible and comparably effective to in-person training models, and T-CETA is found to be as effective as in-person CETA for AYA in Zambia, we aim to expand these technology-driven, cost-effective training and treatment delivery methods across several contexts in sub-Saharan Africa and other LMIC globally.

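### ACASI is said to blind outcome assessment, but the primary outcomes are self-reported by clients who know their arm; it limits interviewer influence and does not blind

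*Protocol article*

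**What the plan says.** In the protocol article, Methods, Randomization and blinding, the claim reads "The use of ACASI will result in the outcome assessments being blinded". The same section says that "Eligible AYA clients will be informed immediately of the result of the randomization", that "the field staff will not be blinded to condition assignment for participants they assess", and that "neither counselors nor AYA clients will be blinded".

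The mode of data collection is set out under Screening and baseline assessment: "Participants can navigate through the questionnaires themselves using a laptop computer", with audio through headphones, and "A research assistant will be positioned nearby in case the participant has any difficulty". The Outcomes section carries this over to the three primary outcomes, which are "administered via ACASI as described in the “Screening and baseline assessment” section". It also names ACASI for two secondary client outcomes, substance use (ASSIST) and aggression/violence (Youth Victimization Scale). It gives no mode for the EQ-5D-Y.

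The Discussion lists as its first limitation that "this trial has a risk of social desirability bias in AYA reporting of symptoms, particularly in the CETA treatment arms". It attributes this to the therapeutic relationship with counselors and offers ACASI, run by research assistants instead of counselors, as the countermeasure. It does not call ACASI blinding there, and it does not list unblinded self-report as a limitation.

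**The concern.** An outcome assessment is blinded when whoever makes the judgement does not know the allocation. In a self-interview that person is the respondent, and here every respondent has been told the arm before any follow-up assessment. The section therefore claims a protection against bias that its own description of the design rules out.

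What is at stake is how the superiority results may be read. TAU clients know that they have not been given the new therapy during follow-up; CETA and T-CETA clients know that they have. If treated clients under-report symptoms, the bias favours CETA and T-CETA over TAU, and the Discussion expects the problem mainly in those arms. A reader or evidence reviewer who takes the blinding sentence at face value would rate this risk too low for all three primary outcomes.

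**Working it through.** **Who knows the arm at follow-up**

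| Role | Knows the arm? | Source in the protocol article |
|---|---|---|
| Client, who supplies every ACASI answer | Yes, told right after randomization | Randomization and blinding; Screening and baseline assessment |
| Field staff, for participants they assess | Yes, after randomization | Randomization and blinding |
| Counselor | Yes, but does not administer the outcome measures | Randomization and blinding; Discussion |
| Data analyst | Stated to be blind | Randomization and blinding |

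ACASI replaces an interviewer who asks and scores. That removes one route for bias, but the only remaining judge of symptom severity is the client, who is unblinded. These sections leave no blinded assessor.

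**The plan's own figure**

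No figure in the document depends on the blinding claim. The superiority calculation matters only because it gives the scale for an illustration. Inputs from Data analysis: effect size 0.5, alpha 0.025 per comparison (taken as two-sided), power 0.80, SD 13.

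- Normal approximation: n = 2(z₀.₉₈₇₅ + z₀.₈₀)² / d² = 2(2.241 + 0.842)² / 0.25 ≈ 76.0, rounded up to 77 per arm.
- With the t distribution: 77.3, rounded up to 78. The stated 78 is reproduced.
- Target effect in CPSS points: 0.5 × 13 = 6.5.

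**Illustration with an assumed reporting shift**

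The document gives no size for reporting bias. The shifts below are assumptions.

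- 0.1 SD: 0.1 × 13 = 1.3 points; 1.3 / 6.5 = 20% of the target effect.
- 0.2 SD: 0.2 × 13 = 2.6 points; 2.6 / 6.5 = 40% of the target effect.

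Suppose the true effect is zero and the shift b (in SD units) favours CETA. The chance that one comparison with TAU is declared significant in favour of CETA is then about 1 − Φ(2.241 − b/SE), with SE = √(1/n_TAU + 1/n_CETA). The table adds the small opposite tail, so that b = 0 gives the nominal 2.5%.

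| Assumed shift b | 78 TAU vs 114 CETA | 100 TAU vs 150 CETA |
|---|---|---|
| 0 | 2.5% | 2.5% |
| 0.1 SD | 6% | 7% |
| 0.2 SD | 19% | 24% |

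For 78 vs 114, SE = √(1/78 + 1/114) = 0.147. At b = 0.2, b/SE = 1.36 and 1 − Φ(0.88) = 0.19. The rate is higher in the larger sample, so more participants would not remove the problem.

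**The case against.** The strongest reply is that the article hides nothing. It says outright that clients and counselors are not blinded, that field staff are not blinded, and that social desirability bias is a risk. Unblinded self-report is unavoidable for symptom scales in a psychotherapy trial. On this view only one sentence is badly worded, and design, sample size and analysis are untouched. Much of this stands: the defect lies in the claim and in what may be concluded from it. Disclosing elsewhere in the section that clients are unblinded, however, contradicts the claim and does not cure it.

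Four stronger readings are tempting, and the document does not support them.

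- **That ACASI gives no protection.** It standardizes administration, removes interviewer scoring and keeps counselors out of the assessment. This answers, at least in part, the mechanism that the Discussion names.
- **That staff influence the answers at follow-up.** The text does not say that the person who told a client the allocation attends that client's follow-up, or that anyone can see the screen. The description of an assistant nearby comes from the screening section.
- **That analyst blinding must fail because counselor data give TAU away.** Treatment as usual control has counselors checking in with TAU clients monthly, and Data analysis does not say how counselor ID is coded for TAU. The masking of labels may be left to a plan that is not shown.
- **That 20 to 40% of the effect will be bias.** That range follows only from the assumed shift.

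**Conclusion.** The statement that ACASI blinds the outcome assessments is wrong as written. It conflicts with the unblinded status of clients and field staff in the same section and with self-completion of all three primary outcomes. This conclusion needs no assumption about the size of the bias.

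The consequence falls mainly on CETA versus TAU and T-CETA versus TAU, which are open-label comparisons on self-report. In T-CETA versus CETA both groups know they are treated and both have a counselor, so bias may partly cancel; its net direction cannot be told from the document. The numerical illustration is conditional on shifts of 0.1 to 0.2 SD, an SD of 13 and, for the rejection rates, a true effect of zero. It shows that modest shifts would matter, not that they will occur. The correction should be made: it costs little and changes what superiority over TAU can claim.

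**What to change.** 1. Under Randomization and blinding, replace the sentence with wording such as: *Outcomes are self-reported by unblinded participants and are not blinded; ACASI limits interviewer influence only.*
2. In the Discussion, name unblinded self-report as a limitation in its own right, beside social desirability.
3. Interpret and report superiority over TAU as an open-label comparison on self-reported symptoms.
4. Optionally, where existing staffing allows, have a research assistant who did not communicate that client's allocation attend the follow-up ACASI. This takes away one cue; it does not create blinding.

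Items 1 to 3 are changes of wording. Item 4 is a rota matter for staff already in place. Sample size, outcomes, models and error rates do not change. The downside is that the stated risk of bias becomes less favourable.
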